#### 15.1.1 Sub-group & interim analysis

No sub-group analyses are planned.

### 15.2 Qualitative analysis

All interviews will be transcribed verbatim (audio recordings will be uploaded and transcribed by an approved Cardiff University supplier via a secure portal for the purpose of transcription and deleted from the portal once transcription is complete) and analysed using Thematic Analysis [48]. A coding framework will be developed which will be closely aligned with the trial specific process evaluation framework and data will be categorised accordingly. Commonly expressed themes as well as unusual cases will be identified. Intervention delivery observations/audio recordings will be coded against key intervention components to assess fidelity of the intervention delivery. All interview transcripts will be checked for accuracy/anonymisation and 20% will be double-coded to check for reliability of the coding framework.

The qualitative analysis will then feed into the overall process evaluation which will be conducted in accordance with the MRC guidance [45] and will use a mixed methods approach. The aim of the process evaluation will be to report on each of the process evaluation components (Reach, Recruitment and Retention, Fidelity and Acceptability, Compliance, Contamination and Context) [45]. Fidelity will be assessed with support from a previously developed CTI fidelity assessment tool (CTI-TS) [46]. Data sources will be mapped against each of these components and data will be triangulated

[figure not shown]

(where relevant) to provide a detailed overview of participants and staff experiences and acceptability of the intervention as well as the delivery methods and fidelity of delivery.

This analysis will ultimately inform understanding of acceptability, views and experiences of the intervention and acceptability of trial, to inform acceptability of a full-scale trial.

### 15.3 Economic evaluation

The broader health and social impacts of the intervention, and associated costs will be considered to inform an economic evaluation in a full-scale trial. In particular, we will: test the feasibility of data collection instruments in capturing costs associated with participants' short-term use of health and community services and broader costs (e.g., criminal justice, welfare costs); test feasibility of using cost logs to capture the costs to deliver the intervention (e.g., staff costs); examine the distribution of the health-related quality of life and capability measures (EQ-5D and ICECAP-A has previously been successfully used in the people experiencing homelessness population [5, 6, 49]) and measure its association with housing stability, physical and mental health. Descriptive statistics (including levels of missing data) for each outcome and cost variable will be reported at each data collection time point and for each intervention group. The patterning and percentage of missing data will inform likely analytical strategy in full-scale trial (e.g., whether multiple imputation is necessary). The distribution of outcome and cost variables will inform likely distributional assumptions to be made when propagating uncertainty through the cost-effectiveness analyses.

An exploratory cost-consequences analysis [50] will report costs alongside consequences for intervention and control groups (this will involve participation of PPI representatives to ensure all relevant costs and consequences are captured). Although cost-effectiveness analyses will be considerably uncertain at this pilot trial stage, we will conduct a short-term (1 year time horizon) cost-utility analysis. Kaplan-Meier estimates of survival probabilities will be combined with the repeated measurements of costs and EQ-5D to obtain mean costs and quality adjusted life years (QALYs) for both intervention and control groups (allowing estimation of the incremental cost-effectiveness ratio) [51]. Scenario sensitivity analysis [52] will be used to identify prices of the CTI intervention at which it would be cost-effective (using NICE threshold) given a range of plausible short-term QALY gains. We will use the cost-utility analysis results to inform value of information (VOI) [53] analyses. These VOI analyses will also assist in identifying the likely key parameters that will drive decision uncertainty and therefore help in planning the design of the full-scale trial.

A review of existing evidence will assist in: 1) identifying suitable modelling frameworks to assess the cost-effectiveness of the CTI intervention over the long-term; 2) identifying the key sources of

[figure not shown]

uncertainty in relation to the probability of the intervention being cost-effective when a long-term time horizon is used. This review and the pilot economic evaluation outlined above will be used in combination to develop an economic conceptual model [54] for the long-term, to be developed at full-scale trial stage. The process evaluation, cost consequences analysis and cost-utility analysis in this pilot trial will inform the optimal time horizon for the economic evaluation alongside the full-scale trial. We will explore using the linked data sources (see section 15.4) to inform longer-term cost-effectiveness modelling in the full-scale trial stage.

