| ICECAP-A                   |                            | X        | x         | x       | x       | x        |                                 |                        |
| AUDIT-C                    |                            | X        | x         | x       | x       | x        |                                 |                        |
| Housing                    |                            | X        | x         | x       | x       | x        |                                 |                        |
| Resource use questionnaire |                            | X        | x         | x       | x       | x        | x                               |                        |

 Taken from the HRA CTIMP protocol template (2016).

[figure not shown]

|                                                 |  |   |         |         |   |         |   |   |
|-------------------------------------------------|--|---|---------|---------|---|---------|---|---|
| Cost log
(intervention and control)          |  |   |         |         |   |         |   | X |
| Criminal Justice                                |  |   |         |         |   |         | x |   |
| Participant interviews                          |  |   | Phase 1 | Phase 2 |   | Control |   |   |
| Staff interviews                                |  |   | x       | x       | x | x       |   |   |
| Interventionist interviews                      |  |   | X       | x       | x | x       |   |   |
| Intervention observations & Fidelity assessment |  |   | x       | x       | x |         |   |   |
| Safeguarding                                    |  | X | X       | X       | X | X       |   |   |
| Withdrawal Checklist                            |  | X | X       | X       | X | X       |   |   |

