### 14.4 Missing, unused & spurious data

The rate of completeness for baseline and follow-up measures will be described. No imputation will be performed.

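### The cost-utility analysis in section 15.3 names an arm-mean estimator with no adjustment for baseline EQ-5D, baseline resource use or prison, at a cost in precision and exposure to chance imbalance

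*Protocol*

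**What the plan says.** Section 15.3 commits to a cost-utility analysis: "we will conduct a short-term (1 year time horizon) cost-utility analysis". It also names how the quantities are built: Kaplan-Meier survival estimates are combined with "repeated measurements of costs and EQ-5D to obtain mean costs and quality adjusted life years (QALYs) for both intervention and control groups", and the ICER is estimated from these. The results have a later use: "We will use the cost-utility analysis results to inform value of information (VOI") analyses, which are meant to help design the full-scale trial. The section gives its own warning: "Although cost-effectiveness analyses will be considerably uncertain at this pilot trial stage".

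The schedule in section 12.1 (Figure 1) has EQ-5D and the "Resource use questionnaire" at baseline and at 3, 6, 9 and 12 months. Sections 9.1.5 and 14.1 stratify randomisation by prison and by nothing else.

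Section 15.1 uses baseline data and allows for nesting within prison, but only for the effectiveness outcomes. Section 15.3 has no matching statement for costs or QALYs. It neither calls its estimates unadjusted nor rules adjustment out.

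**The concern.** The named estimator gives one mean QALY and one mean cost per arm and then takes differences. Baseline EQ-5D is the first point on each participant's one-year curve and is likely to be correlated with the later points. If one arm happens to start healthier, part of that head start is therefore counted as QALY gain. Stratifying by prison does not balance EQ-5D or resource use, and with 40 per arm a visible imbalance is quite possible.

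There is also a loss of precision. Ignoring a correlated baseline value leaves the incremental QALY with more variance than the collected data require. Value of information depends on both the centre and the spread of the incremental estimates, so both effects reach an output that is meant to shape the next trial.

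**Working it through.** **Inputs from the protocol.** 80 participants, 40 per arm (section 14.3); 40% drop-out at final follow-up (synopsis), so 40 × 0.6 = 24 per arm; EQ-5D at 0, 3, 6, 9 and 12 months (Figure 1); one-year horizon (section 15.3).

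**Assumptions.** The protocol gives no EQ-5D SD and no correlation between visits. I take SD 0.2 to 0.4 and an equal correlation r of 0.2 to 0.7 between any two visits. Deaths and missing data are ignored.

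**The plan's own figure.** Section 15.3 states no QALY, cost or ICER figure. The only precision figure in the protocol, in section 14.3, reproduces with n = 80: 1.96 × √(0.5 × 0.5 / 80) = 0.110 and 1.96 × √(0.75 × 0.25 / 80) = 0.095.

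**Step 1: chance baseline difference.** SE = SD × √(2/n).
- 40 per arm: 0.2 × √(2/40) = 0.045, up to 0.4 × √(2/40) = 0.089.
- 24 per arm: 0.058 to 0.115.
- The probability of an absolute difference above 0.05 is 26% to 58% at 40 per arm and 39% to 67% at 24 per arm.

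The 24-per-arm figures describe an analysis of completers only. An analysis that uses every observed visit lies between the two.

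**Step 2: how much passes into the QALY.** The trapezoidal weights over one year are 0.125, 0.25, 0.25, 0.25 and 0.125. The expected change in the incremental QALY per unit of baseline difference is b = 0.125 + 0.875r.

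**Step 3: precision.** The squared weights sum to 2 × 0.125² + 3 × 0.25² = 0.21875. In units of SD², the variance of an individual's QALY is V = r + 0.21875(1 − r). Regressing on baseline removes the fraction b²/V, so the ratio of adjusted to unadjusted SE is √(1 − b²/V). At r = 0.5: b = 0.5625, V = 0.609, b²/V = 0.52, ratio 0.69.

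| r | b | SE ratio | Shift from a one-SE imbalance, 40 per arm (SD 0.2 to 0.4) | Same, 24 per arm |
|---|---|---|---|---|
| 0.2 | 0.30 | 0.87 | 0.013 to 0.027 | 0.017 to 0.035 |
| 0.3 | 0.39 | 0.82 | 0.017 to 0.035 | 0.022 to 0.045 |
| 0.5 | 0.56 | 0.69 | 0.025 to 0.050 | 0.032 to 0.065 |
| 0.7 | 0.74 | 0.54 | 0.033 to 0.066 | 0.043 to 0.085 |

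**Step 4: simulation check.** 20,000 trials with 24 per arm, SD 0.3, r = 0.5 and no true difference gave:
- mean unadjusted increment 0.0001, so no systematic bias;
- SD of the increment 0.068 unadjusted and 0.047 adjusted (ratio 0.70);
- dependence on the baseline difference 0.57 QALY per unit unadjusted and about 0.01 adjusted.

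**Costs.** No cost SD and no correlation between baseline and later resource use is given, so no figure can be derived.

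**The case against.** The strongest reply is that covariates are commonly left to an analysis plan. Section 15.1 defers statistical detail to a SAP that is not shown, and section 15.3 never says that adjustment is excluded. That stands as a limit on certainty. But section 15.3 does more than stay silent: it names a specific estimator that yields arm means and says that the ICER follows from them. It refers to no further plan. If adjustment is intended, the named method points the other way.

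Four stronger readings are tempting, and the protocol does not support them.
- **The incremental QALY is biased.** It is not, in the systematic sense. Allocation is randomised, and a one-SE imbalance is ordinary sampling error that a correct interval already covers. What remains is conditional imbalance and avoidable variance.
- **A baseline difference transfers in full.** It transfers in part. Baseline is measured in prison and follow-up is planned for after release, so the correlation, and with it the transfer, may lie at the low end.
- **The price scenarios inherit the problem.** Section 15.3 runs these over a span of assumed QALY gains, so they do not hang on the observed increment. The documented links are to the ICER and the value of information work.
- **Baseline adjustment deals with the 40% drop-out.** It does not. Kaplan-Meier weights address death and not missed questionnaires, but a regression on complete individual QALYs would itself discard men with partial follow-up. Section 14.4 ("No imputation will be performed") concerns missing data and says nothing about baseline adjustment.

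It is also fair that the progression criteria in section 5.1 contain no economic result, and that prison terms use up degrees of freedom in a small sample.

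**Conclusion.** The point holds as a choice of a less efficient method when a better one is available from data already being collected. For QALYs, chance imbalance at baseline carries over at 0.30 to 0.74, and a one-SE imbalance is worth about 0.013 to 0.066 QALY at 40 per arm. The standard error would fall to 0.87 to 0.54 of its unadjusted value, or 0.69 at a correlation of 0.5. All of this rests on the assumed SD of 0.2 to 0.4, equal visit correlations of 0.2 to 0.7, and no allowance for deaths or missing data. For costs the direction of the argument is the same, but the size is unknown.

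Severity is low. The protocol itself treats the cost-effectiveness results as highly uncertain, and they do not decide progression. The reason to act is that they inform the value of information analyses used to plan the full trial.

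**What to change.** In section 15.3, state that the incremental QALY is adjusted for baseline EQ-5D and prison, and the incremental cost for baseline resource use and prison. Use a method that keeps participants with partial follow-up. One example is a repeated-measures model for the follow-up visits or intervals with arm, time, arm by time, the baseline value and prison; its baseline-adjusted arm means are then weighted by Kaplan-Meier survival. Such a model needs no imputation, so it fits section 14.4. It still relies on assumptions about why follow-up is missing.

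Carry the adjusted increments and their uncertainty into the ICER and the value of information analyses. Report the unadjusted Kaplan-Meier arm means as a sensitivity analysis. If a separate plan already specifies adjustment, section 15.3 should say so.

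The cost is a few sentences, slightly more analysis work and a few degrees of freedom (four for five prisons, plus one for the baseline value). No new data are needed.

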#### 15.4 Routine data analysis

We will review existing routine data sources that could be used to assess outcomes at the main stage trial. Provisional outcomes of interest (see logic model in Appendices) include housing stability, criminal justice contacts, alcohol and substance use, and mental health. We will attempt to harmonize potential data sources so that similar outcomes can be measures from across the devolved UK nations. based on this review, data owners will be contacted to assess whether data are accessible for linkage-based studies, and any practical and financial implications if accessing these data. We will also work with data owners to develop trial materials, such as consent questions and participant information sheets, which meet their requirements to enable access to data for the main stage trial without the need for these to be further developed. The review will also seek to explore potential codes within data sources that align with measurable outcomes of interest, i.e., diagnosis codes for hospitalisations due to substance use.

In tandem with this data exploration and engagement activity, we will also be conducting test data linkages to healthcare data sets in England and Wales, and criminal justice data. Test linkages will allow us to assess the percentage of participants who consent to have their data linked and the percentage of data records which can be linked successfully with these data providers. We will generate summary statistics of the completeness of data needed to undertake linkage, i.e., percentage of people providing personal details. As each data owner uses different data matching methods when extracting records, information on the proportion of people from the original trial cohort who we are able to link to will aid in assessing the extent to which linkage at a full trial will generate samples with enough power to detect intervention effects.

De-identified healthcare data will be accessed via NHS England and the Secure Anonymised Information Linkage (SAIL) databank, in England and Wales respectively. Applications to access healthcare data will be made to NHS England via the Data Access Request Service and to SAIL via their Information Governance Review Panel. Information requested from NHS England and SAIL will be

[figure not shown]

limited for the purposes of a test linkage to records related to periods spent in hospital, use of accident and emergency services, outpatients’ services, and death records [55]. We will request data from 5-years prior to enrolment in the study, to assess the potential of linkage to develop baseline healthcare use estimates, up to the latest data available, to assess the use of linkage to evaluate difference in health outcomes between study arms.

We will also seek to link to criminal justice data via the Ministry of Justice Data Lab (‘the Lab’). The Lab is a service operated by the Ministry of Justice that links details of clients engaging with third sector organisations and provides summary reports of re-offending rates for clients—compared to a matched comparison group that the Lab generates from the wider prisoner population. As the Lab’s services may conflict with trial procedures, such as having two trial study arms and the requirement that summary reports be published on the MoJ website, the test linkage to criminal justice data may not occur if deemed incompatible with study goals.

To link records, personal details will need to be shared with data owners, including name, date of birth, gender, and postcode. It may help data owners if unique identification numbers used by their computer systems are provided; therefore, Police National Computer number and NHS number will also be collected and shared with the appropriate data owner. We will use consent questions and participant information materials based on previous studies from the CTR.

The trial Data Manager will be responsible for the processing of personal data prior to sending it to relevant data owners. Only pre-approved secure methods will be used to transfer personal data between the CTR and data owners. Trial researchers will have access to either aggregated data reports (in the case of the MoJ Data Lab) or de-identified data which will be accessed via a secure gateway (SAIL Gateway)—see data flow diagrams in Appendices.

16 Data Management

A Data Management Plan (DMP) and Qualitative data collection and Analysis Plan (QAP) will be developed to outline the different types of data being collected, collection methods, processing of data, data storage and data sharing. The DMP will include details of the management of the following source data:

|            |             |
|------------|-------------|
| Trial data | Source data |
|------------|-------------|

[figure not shown]

|                                  | Screening | CRF | Electronic
health data | routine
criminal
justice data | Participant interviews | Staff interviews | Observational
notes/audio recordings | Safeguarding | Withdrawal |
|----------------------------------|-----------|-----|---------------------------|-------------------------------------|------------------------|------------------|-----------------------------------------|--------------|------------|
| Recruitment                      | x         |     |                           |                                     | X                      | X                |                                         |              |            |
| Health                           |           | X   | X                         |                                     | X                      | X                |                                         |              |            |
| Mental health                    |           | X   | X                         |                                     | X                      | X                |                                         |              |            |
| Substance misuse                 |           | x   | x                         |                                     | X                      | X                |                                         |              |            |
| Police & MoJ
contact          |           |     |                           | x                                   | X                      | X                |                                         |              |            |
| Intervention
Engagement       |           |     |                           |                                     | X                      | x                | x                                       |              |            |
| Intervention
content delivery |           |     |                           |                                     | X                      | X                | X                                       |              |            |
| Safeguarding                     |           |     |                           |                                     |                        |                  |                                         | X            |            |
| Withdrawal                       |           |     |                           |                                     |                        |                  |                                         |              | x          |

Source Data is defined as “All information in original records and certified copies of original records of clinical findings, observations or other activities in a trial necessary for the reconstruction and evaluation of the trial. Source data are contained in source documents.” There is only one set of source data at any time for any data element, as defined in site source data agreement.

16.1 Data collection

Data will be collection directly from participants, staff and through secure data providers. Data will be collected either via paper, electronic, audio recordings or observation notes form the intervention delivery. Any paper based data collection will be securely transported and entered on the trial database on return to the office, personal details will be shared securely with data providers, audio

[figure not shown]

recordings will be uploaded to a secure portal for secure transcription and any hand written observational notes will be word processed as soon as possible.

